### Power analyses, data reduction and statistical analyses

The following effect sizes for power calculations are based on studies that included outcome variables that are of central relevance to our intervention and most closely approximated the methods for the present study.

#### Physical activity and BMI

A study of brief CBT intervention for increasing exercise and reducing BMI in a sample with serious mental illness (Brown and Chan, 2006) demonstrated an increase in exercise for the intervention compared with no change for controls [large effect (Cohen's *d* = 0.89)]. There was a significant difference in BMI change for the intervention compared with controls (*d* = 1.19). Our pilot data are consistent with these findings; thus, we estimate a large effect for improvement in physical activity (*d* = 0.70–0.89).

#### Nutritional consumption and lipid levels

Based on the finding of improved nutrition in response to a computer-based nutritional intervention relative to a control group (O'Brien and Palfai, 2016), we calculated a medium effect size (*d* = 0.54). Based on findings of improved lipids in response to a community-based weight management and nutrition program (Graffagnino et al., 2006), we calculated a moderate effect (*d* = 0.50). This study is consistent with a qualitative review (Laederach-Hofmann et al., 2008) that indicated long-term positive effects of weight management on lipids.

#### Sleep intervention

In an RCT of 168 sexual assault victims with PTSD, IRT resulted in large improvements in number of nights with disturbing nightmares (d = 1.24) and total number of weekly nightmares (*d* = 1.27), and a medium effect for improved sleep quality (*d* = 0.67), compared with waitlist (Krakow et al., 2001). Our pilot data indicate a large effect for improved sleep quantity (*d* = 1.41). Therefore, we estimate effects for sleep quantity and quality outcomes to range from 0.67 to 1.41.

#### Improved blood pressure

A study that examined the effects of an exercise program on blood pressure (Morris et al., 2021) evidenced a moderate effect for SBP (*d* = 0.60) and a large effect for DBP (*d* = 0.83). These findings are consistent with systematic reviews (Aucott et al., 2009; Laederach-Hofmann et al., 2008) that indicate long-term positive effects of weight loss studies on BP. Our pilot data supports a moderate effect for DBP in the PTSD population (*d* = 0.51).

#### Improved CVD markers

In a meta-analysis examining HRV in PTSD, a small subset of studies was identified that examined changes in HRV as a treatment outcome (Nagpal et al., 2013). A range of moderate to large effects was evident for the respective studies and measures of HRV, with a large overall effect (*d* =1.89). To date, we are not aware of any published studies in the PTSD population that have attempted to intervene on arterial stiffness or endothelial function. Therefore, our effect size estimates come from a broader range of studies that examined behavioral interventions with these outcomes. Cavero-Redondo et al. (2021) conducted a meta-analysis of exercise interventions and the effects on arterial stiffness, with an overall moderate effect (*d* = 0.56). A meta-analysis of exercise studies and endothelial function (Lee et al., 2018) indicated that low-moderate intensity aerobic exercise produced desirable improvements in endothelial function (*d* = 0.55).

#### Summary

Completing 162 protocols (81 per condition) with minimum power of 80% and alpha level of 0.05 will permit detection of a moderate effect of 0.47 or greater (Cohen, 1988). Therefore, this sample size would permit detection of the smallest effect estimated above for lipids (*d* = 0.50) and will be conservative for the projected large effects for some of the estimates above. Participants in the health behavior intervention condition (experimental group) are considered treatment completers if ≥75% of sessions are attended.

#### Data analysis plan

Preliminary analyses will be conducted to examine distributions, detect outliers, and compare the study groups on demographic variables, comorbid psychopathology, type of trauma therapy received, smoking, and alcohol use. Based on the randomization, no differences for demographic (e.g., age, gender) or other baseline comparison variables are expected. In addition, gender is not predicted to interact with the main study effect (condition). If there are group differences in any of the baseline comparison/control variables, the respective variable(s) will be treated as a control in the analyses.

A between-groups approach is used, with study condition as the independent variable (IV) and changes in the outcomes as the dependent variable(s) (DVs). The outcomes will be analyzed using linear mixed-effects regression. This approach is recommended for between-group longitudinal trials with follow-up time points to model changes over time, to incorporate all available data at each time point, and to account for non-independence of observations inherent in repeated-measures data (Verbeke and Molenberghs, 2000). A piecewise model will be specified to model change during distinct time periods of the trial (Raudenbush and Bryk, 2002). Separate slopes will be provided for the pre- to post-treatment phase, and each follow-up point (pre- to 6-month follow-up, and pre- to 12-month follow-up). Multivariate analyses will be used for each hypothesis to control for type 1 error by testing the DVs together. Significant multivariate effects will be followed with univariate tests.

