## Methods

### Participants

We plan to randomize a total of 212 participants, ages 18 and over, to the two study conditions. Anticipated demographics of the overall sample, based on current data from proposed recruitment sites and prior studies recruiting from the PTSD population, are ages 37 ± 10 (mean ± SD), approximately 72% female, avg. of 12th grade education ± 3 years, and race/ethnicity composed of 64% Caucasian, 21% Hispanic-White, 10% African-American, 3% Caribbean Black, and 2% Hispanic-Non-White. Adults ages 18 and older are recruited from the community, local clinics, and via online advertisements. Criteria for inclusion are: PTSD or subthreshold PTSD [evidenced by ≥ 4 PTSD symptoms (including ≥ 1 re-experiencing symptom) endorsed as 2 or higher (moderately bothersome) on the Posttraumatic Stress Checklist (PCL-5)], the presence of at least one health risk (low physical activity, nutrition does not meet standard recommendations, overweight, sleep disruption), and ability to exercise at a moderate level. Concurrent trauma-focused psychotherapy is required through the 12-week intervention phase of the project and is provided by the project if the participant is not already receiving trauma-focused therapy in the community. On an ongoing basis, the project coordinator verifies the therapy and frequency. Although chronic illnesses are not exclusionary, medications for controlling lipids or blood pressure (e.g., beta blockers, diuretics, ACE inhibitors, statins, PCSK9 inhibitors) are exclusionary, as they would impact the lipid and blood pressure outcomes. Participants may be considered if they are able to consult with their medical provider about temporarily discontinuing these medications long enough for the medication to not be active in the system. Comorbid psychiatric conditions (e.g., depression, personality disorders, substance use disorders) are not exclusionary, as this would result in an unnaturally narrow selection of participants with PTSD. Consistent with standards for intervention studies in PTSD (Mulick and Naugle, 2010; Resick et al., 2002, 2015), those on psychopharmacological medications will be included if the regimen has been maintained as stable for ≥2 months prior to enrollment. This study is approved by the appropriate University Institutional Review Board (IRB). Written informed consent is obtained from all participants at the time of the first outcome assessment (baseline) by the laboratory research assistant(s). As with any human research, a participant may discontinue either intervention condition or any other aspect of the longitudinal study at any time, regardless of the reason.

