### Procedures

#### Recruitment and enrollment

Participants are recruited from university and community-based clinics, private practices, and from the community using written and online notices/flyers. Locations for recruitment within the community using written flyers include community college campuses, bus/train stops, parking garages, public bulletin boards, public libraries, public restrooms, convenience stores, shopping centers/grocery stores with community bulletin boards, laundromats, religious centers (churches), community centers, public parks, and recreation centers. Online notices for the study are posted on Craigslist, Facebook, and Instagram. Participants are also recruited by other participants within the study. Potential participants call a private central phone number or respond to the study email address to express interest in the study. Volunteers are then screened by phone to assess basic study inclusion and exclusion criteria and to provide additional details about the study. Randomization to study condition is performed by the project coordinator following the initial phone contact (using the flip of a coin). Neither the participants nor the investigators are blinded for this trial. At the baseline/pre-intervention assessment, informed consent and additional screening assessments are administered to further evaluate and verify eligibility based on PTSD symptoms and the presence of at least one risk factor targeted by the intervention (e.g., physical inactivity, overweight status, sleep difficulties). All records are kept confidential. A list of participant names linked to their code numbers is kept in a secured file and accessed by study coordinators for project-related communications. Only code numbers are used to organize participant study data. The coded project data are kept in a separate secured file. Participant compensation consists of a $50 gift card for each of the pre-, post-, and follow-up assessment sessions, and a $10 gift card for each intervention session completed by the participant.

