#### Training of study interventionists

The interventionists for the project are advanced doctoral students with experience delivering CBT-based health interventions and/or trauma-focused therapies (depending on the protocols they are trained to conduct). The health behavior interventionists are familiar with the healthy lifestyle intervention literature and develop a thorough understanding of the protocol for PTSD patients by reviewing the manual and meeting with the PI for training. Interventionists are encouraged to meet with the PI throughout intervention delivery to affirm their knowledge and confidence with the protocol and address any questions that might relate to participant-specific presentations.

For interventionists who conduct the standard trauma therapies, the PI reviews evidence-based conceptual and intervention models of trauma-focused treatment for PTSD, including Cognitive Processing Therapy (Resick et al., 2002; Resick and Schnicke, 1992), Prolonged Exposure Therapy (Foa et al., 2007; McLean and Foa, 2024), and as applicable for participants with a presentation consistent with the literature on complex-PTSD, Contextual Trauma Therapy (Gold and Quiñones, 2020). Trauma therapists are encouraged to review treatment-specific readings for the various models of treatment reviewed during training and meet with the PI and project coordinators (designated as lead interventionists) to discuss treatment options for assigned participants. Trauma therapists select treatment approaches based on the clinical presentations of participants and collaboration with participants about the various options for care. Given the literature suggesting increased rates of drop-out in exposure-based treatment, it was imperative that trauma therapists have a strong rationale for this approach, a deep understanding of its implementation, and the ability to educate the participant about the treatment delivery (Imel et al., 2013). Trauma therapists are invited to discuss their approaches to treatment, ask questions about intervention implementation and participant clinical presentations, as well as discuss relevant research on PTSD treatment during monthly research lab meetings, in one-on-one meetings with the PI, and in peer supervision meetings with the research coordinators.

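### The covariate rule takes in trauma therapy type, which for project-supplied therapy is apparently chosen after allocation and so is not a baseline variable

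*Protocol article*

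**What the plan says.** The Data analysis plan opens with preliminary analyses that "compare the study groups on demographic variables, comorbid psychopathology, type of trauma therapy received, smoking, and alcohol use". It continues: "Based on the randomization, no differences for demographic (e.g., age, gender) or other baseline comparison variables are expected". For any baseline comparison or control variable on which the groups differ, "the respective variable(s) will be treated as a control in the analyses". No test or threshold for a difference is given, and nothing says how the control enters the model. The outcome model is a piecewise linear mixed-effects regression, with changes in the outcomes named as the dependent variables.

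Four statements elsewhere in the protocol bear on therapy type:

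- Participants: trauma therapy "is provided by the project if the participant is not already receiving trauma-focused therapy in the community".
- Training of study interventionists: "Trauma therapists select treatment approaches based on the clinical presentations of participants and collaboration with participants about the various options for care". The options named are Cognitive Processing Therapy, Prolonged Exposure and, for complex presentations, Contextual Trauma Therapy.
- Recruitment and enrollment: "Randomization to study condition is performed by the project coordinator following the initial phone contact", which is before consent and the baseline visit.
- Recruitment and enrollment: "Neither the participants nor the investigators are blinded for this trial".

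**The concern.** Therapy type stands in the same list as age, smoking and alcohol use, and the same paragraph expects balance because of randomisation. That reasoning works for characteristics fixed before allocation. It does not work for a treatment decision taken afterwards by people who know the arm.

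The comparison set out under Study design is the program added to usual care psychotherapy. A contrast unadjusted for therapy received estimates this validly, even if being offered the program changes which therapy people choose. Adjusting for therapy received replaces it with a contrast conditional on something that allocation may have affected and that also depends on clinical presentation. The resulting bias can go in either direction.

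The trigger makes this worse. If arm has no influence on the choice, adjustment is harmless and, at a 5% test, fires in about 5% of trials. If arm does influence the choice, the rule fires more often, and that is when adjustment can mislead.

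**Working it through.** **1. Timing.** For someone already in community trauma therapy, type can predate allocation. For someone on project therapy, allocation follows the phone contact, consent comes at the baseline visit, and the therapist then selects the model. That the choice follows allocation is inferred; no section dates it.

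**2. Does the adjustment reach the program effect?** Let D_t be the arm difference at visit t, b the covariate coefficient and ΔT the arm difference in therapy share. With complete data, an arm main effect and arm-by-visit terms, a main-effect covariate gives D_t − bΔT at every visit. The change contrast is (D_t − bΔT) − (D_0 − bΔT) = D_t − D_0, which is unchanged. A simulated four-visit mixed model with all inputs at their maximum agreed: the three condition-by-time coefficients were 0.0202, −0.0203 and −0.0660 both before and after adding therapy type. Bias of about 0.1 SD appeared only when a therapy-by-time term was added. Regressing change scores on arm and therapy has the same effect, and the wording about changes as dependent variables permits that.

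**3. Size when it does reach it.** The documents give no inputs, so all of these are assumed:

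- outcome SD 1, true program effect 0, therapies equally effective, and one therapy's share averaging 50%;
- an arm-driven shift of 10 or 30 points in that share among project-therapy participants;
- an unmeasured presentation factor with odds ratio 2–3 per SD on choice and 0.3–0.5 SD on outcome.

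The unadjusted contrast is correct (0). Regression on arm plus therapy received gives the false effects in the table (absolute values). The sign is negative if the factor improves the outcome and positive if it worsens it. With no shift, the bias is at most 0.001.

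**4. How often the check fires.** Assume a two-sided 5% test on 212/2 = 106 per arm. The SE of the difference in shares is √(2 × 0.5 × 0.5/106) = 0.0687, so the critical difference is 1.96 × 0.0687 = 0.1346. With half on project therapy, a 10- or 30-point shift is 5 or 15 points across the whole arm. For 15 points, Φ((0.15 − 0.1346)/0.0687) = Φ(0.22) = 0.59.

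**5. Averaged over firing.** The simple product is the firing rate times the bias if adjusted. With half on project therapy this is 0.112 × 0.009 = 0.001 up to 0.590 × 0.065 = 0.038. It is somewhat low, because the unadjusted estimates that are kept come from trials selected for a small observed imbalance. The rule's full bias is g × E[D; |D| > 0.1346], where g is the bias if adjusted divided by the whole-arm shift, and D is normal with mean equal to that shift and SD 0.0687.

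- 5 points: E = 0.05 × 0.109 + 0.0687 × φ(1.23) − 0.0006 = 0.0177. With g = 0.18–0.44 the bias is 0.003–0.008.
- 15 points: E = 0.15 × 0.589 + 0.0687 × φ(0.22) = 0.115. With g = 0.187–0.433 the bias is 0.021–0.050.

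| On project therapy | Shift (points) | Fires | Bias if adjusted (SD) | Simple product | Whole rule |
|---|---|---|---|---|---|
| All | 10 | 31% | 0.019–0.045 | 0.006–0.014 | 0.010–0.025 |
| All | 30 | 99% | 0.056–0.134 | 0.056–0.133 | 0.056–0.134 |
| Half | 10 | 11% | 0.009–0.022 | 0.001–0.0025 | 0.003–0.008 |
| Half | 30 | 59% | 0.028–0.065 | 0.017–0.038 | 0.021–0.050 |
| Quarter | 10 | 6% | 0.005–0.011 | 0.0003–0.0007 | 0.001–0.003 |
| Quarter | 30 | 19% | 0.014–0.033 | 0.003–0.006 | 0.006–0.015 |

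**6. Scale.** The power Summary's detectable effect is 0.47, so with half on project therapy the bias if adjusted is 0.009/0.47 = 2% to 0.065/0.47 = 14% of it. The standard error of a two-group difference at 81 per arm is √(2/81) = 0.157 SD.

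**The case against.** The strongest reply is that the adjustment sentence covers only variables it calls baseline. If project-supplied therapy type is not a baseline variable, then read literally the rule leaves it out, and comparing arms on it in preliminary analyses is close to plain description. This leaves real doubt. However, the plan puts therapy type in the comparison list, gives no separate rule for it, and refers back to that list when it states what becomes a control. The natural reading includes it.

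The second reply is that harm needs several conditions at once: therapy supplied by the project, the choice made after allocation, arm influencing the choice, an unmeasured factor driving both choice and outcome, the check firing, and the covariate entering the model for change. This stands, and it is why the point is minor. How the covariate enters is ordinary analysis-plan detail. What the article does fix is that therapy type is compared alongside baseline variables under an adjust-if-different rule.

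A reader might go further and infer that the arms will differ in therapy choice, or that leaving the choice to therapist and participant is itself a flaw. The documents support neither. The stated basis for choosing is clinical presentation and collaboration with the participant, with no mention of arm, and individualised choice is legitimate usual care.

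**Conclusion.** The point holds in a limited form. Therapy type is treated as a baseline variable, but for project-supplied therapy it is apparently decided after open allocation. On the natural reading, the rule could condition the randomised contrast on it.

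It would be too strong to say that the plan's adjustment biases the program effect. That needs an arm-driven shift in choice, which no section shows, and a model in which therapy type acts on change. Otherwise the estimate is unaffected. With half on project therapy (an assumed share), the bias is 0.01–0.07 SD when adjustment occurs. It averages about 0.001–0.04 SD by simple product, or 0.003–0.05 SD for the whole rule, against a sampling standard error near 0.16 SD. Only the case with everyone on project therapy and a 30-point shift reaches 0.06–0.13 SD, and its top needs every input at its maximum. Severity is minor; the change is worth making because it costs almost nothing.

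**What to change.** In the Data analysis plan:

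- exclude trauma therapy type from the covariate rule;
- report therapy type by arm as a post-randomisation description;
- keep the primary contrast unadjusted for it;
- label any model adjusted for it as a sensitivity analysis.

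If a therapy covariate is wanted, use therapy source at entry: already in community trauma therapy, or project-supplied.

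The cost is a text edit. Procedures do not change, and little or no new data are needed, since "On an ongoing basis, the project coordinator verifies the therapy and frequency". The downside is that a chance imbalance in therapy type is described rather than adjusted for in the primary analysis.

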#### Demographic measures

Basic demographic information, including age, race, ethnicity, family income, marital status, and education level, is assessed by self-report.

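### Covariates enter the model only if the arms are found to differ, and the candidates include therapy type, which for project-provided therapy is chosen after allocation

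*Protocol article*

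**What the plan says.** The Data analysis plan section opens with preliminary analyses that will "compare the study groups on demographic variables, comorbid psychopathology, type of trauma therapy received, smoking, and alcohol use". It then says: "Based on the randomization, no differences for demographic (e.g., age, gender) or other baseline comparison variables are expected". The rule follows: "If there are group differences in any of the baseline comparison/control variables, the respective variable(s) will be treated as a control in the analyses". No test or threshold for a difference is given, and no other section of the article names a fixed covariate set or restricts candidates to variables that precede allocation.

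On timing, Recruitment and enrollment has the project coordinator allocate by coin flip after the first phone contact, before consent and the baseline visit, and adds: "Neither the participants nor the investigators are blinded for this trial". On therapy, the Participants section says trauma-focused treatment "is provided by the project if the participant is not already receiving trauma-focused therapy in the community". For those whom the project treats, Training of study interventionists says: "Trauma therapists select treatment approaches based on the clinical presentations of participants and collaboration with participants about the various options for care".

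**The concern.** There are two problems of different kinds.

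First, the rule selects covariates by observed imbalance and not by their relation to the outcome. By the plan's own expectation, a difference in a true baseline variable is chance. A weak predictor that happens to be imbalanced goes in, and a strong one that happens to be balanced stays out. The primary model cannot be written down before the data are examined, and precision that a fixed set of good predictors would give is not secured.

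Second, the rule treats therapy type as a baseline variable. For project-treated participants it is set after allocation, by people who may know the arm. An arm difference in therapy type could then be a consequence of assignment, and the rule adjusts for it exactly when such a difference appears. At stake is the comparison the trial exists to make: the effect of adding the health behavior program to standard trauma therapy.

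**Working it through.** The plan gives no figure for this rule, so there is none to reproduce. The inputs below come from the article or are marked as assumed.

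**Number of candidates.** The Demographic measures section says: "Basic demographic information, including age, race, ethnicity, family income, marital status, and education level, is assessed by self-report". That is 6. The Data analysis plan adds gender (1), comorbid psychopathology (at least 1), type of therapy (1), smoking (1) and alcohol use (1): 6 + 1 + 1 + 1 + 1 + 1 = 11. Counting only the five named domains gives 5. Leaving out therapy type, since it is not a true baseline variable for everyone, gives 10.

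**Chance that the rule fires under sound randomisation.** With k independent comparisons at level a, the probability of at least one difference is 1 − (1 − a)^k. Both a and independence are assumptions.

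| k | a = 5% | a = 10% |
|---|---|---|
| 5 | 1 − 0.95^5 = 23% | 1 − 0.90^5 = 41% |
| 10 | 1 − 0.95^10 = 40% | 1 − 0.90^10 = 65% |
| 11 | 1 − 0.95^11 = 43% | 1 − 0.90^11 = 69% |

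Income, education, marital status, race and age are likely to be correlated. A simulation with 81 per arm, 11 variables, an assumed pairwise correlation of 0.3 and a 5% threshold gives about 37%.

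**What chance selection costs.** I simulated 81 per arm (the completer number in the Summary of the power section), 11 independent baseline variables jointly explaining 10% to 50% of outcome variance (assumed), and adjustment for those with p < 0.05. The treatment estimate was unbiased and type I error did not exceed 5%. With 30% explained and a true d of 0.50, power was about 90% under the rule, 89% unadjusted and 95% with all 11 fixed in advance. The rule therefore secures little of the available precision.

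**Therapy type as a post-allocation variable.** Assume a binary therapy type, 40% on it in the control arm, an effect of that type on the outcome of 0.5 residual SD, and a total effect of assignment of 0.50. If p is the share on that type in the experimental arm, always adjusting moves the target to 0.50 − 0.5 × (p − 0.40). The last three columns are simulated (81 per arm, 4,000 runs, chi-square p < 0.05 as the trigger).

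| p | Always adjusted | Rule adjusts in | Mean estimate, rule | Power, rule |
|---|---|---|---|---|
| 40% | 0.50 | 4% | 0.50 | 87% |
| 50% | 0.45 | 25% | 0.48 | 83% |
| 60% | 0.40 | 72% | 0.42 | 73% |
| 70% | 0.35 | 97% | 0.35 | 56% |

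Unadjusted power was 86–87% throughout. If that type of therapy worsened the outcome by the same amount, the adjusted target at p = 60% would be 0.50 + 0.5 × 0.20 = 0.60, so the direction can reverse. With no arm difference in therapy choice there is no bias. The article gives no therapy shares or therapy effects, so these figures show a mechanism and do not predict this trial.

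**The case against.** The strongest defence is that adjusting for a prognostic variable that is imbalanced removes the chance bias of that particular trial. This stands: over repeated trials the rule is unbiased for true baseline variables, and in simulation it does not inflate type I error. A reader might infer that the inference is invalid because standard errors ignore the selection step, or that the model changes for no reason. Neither is supported.

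A reader might also infer that the covariates would vary from one outcome to another. The text does not say so. Selection uses only the comparison of arms, and a selected variable becomes a control in the analyses generally, so the rule gives one set per trial.

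On therapy type, the article says the approach follows clinical presentation and discussion with the participant. Nothing says that the arm influences it, and for participants already in community therapy the type may precede allocation. So the stronger reading, that adjustment necessarily breaks the randomised comparison, goes beyond the document. What stands is that allocation is unblinded and comes first, so nothing prevents such an influence.

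Finally, one could argue that an effect above and beyond standard therapy calls for holding therapy type constant. But the type is selected on clinical presentation, which may itself predict outcome. Conditioning on it after allocation does not by itself deliver that effect, and doing so only when the arms differ leaves the target of estimation to the data.

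**Conclusion.** The concern holds in two parts. For true baseline variables, the rule leaves the model unspecified until the data are seen and gives up precision; it does not bias the estimate. The 43% rests on 11 variables, independence and a 5% threshold, none of which the article fixes. A range of 23% (five variables) to 69% (11 variables at a 10% threshold) is a fairer picture, and correlation among the variables lowers each figure. For therapy type, bias in either direction is possible but not certain. It requires that therapy choice among project-treated participants differ by arm and that it affect the outcome. This is a rule that the article states, not detail left to another document, and it should be corrected before outcome data are examined.

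**What to change.** Delete the imbalance-triggered rule. Name, for all outcomes and whatever the observed balance, a small set of prognostic covariates measured before allocation or unaffected by it. Age and gender are examples; smoking and therapy source (project or community) could be added if recorded as of before the coin flip. The final choice should rest on the investigators' knowledge of what predicts the outcomes.

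Handle the baseline outcome once. The planned piecewise mixed model of change already contains it, so either keep it as a repeated measure (for example with a common baseline mean constrained across arms) or use it as a covariate with only post-baseline values as outcomes.

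Present baseline characteristics by arm descriptively, without tests. Report therapy type and amount received by arm descriptively, or in a sensitivity analysis labelled as such, and keep them out of the primary effect model.

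The cost is analysis-plan wording, plus confirming that smoking and therapy source are captured as of before allocation. The number of participants does not change.
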